## Discussion

3

Although loneliness is currently receiving increased attention as a factor that is relevant to public health, and the fact that people with depression can be considered a risk group, there have been no studies to date on the relevance of loneliness to the treatment of depression. Thus, this naturalistic prospective study provides important insights into whether and to what extent loneliness is relevant for the treatment of depression. A variety of self-report instruments, clinical interviews, routine data, and biosampling approaches are employed for this purpose. The multimethod and longitudinal approach reduces measurement method variance; however, the predominantly exploratory consideration of secondary outcomes and biosamples also carries the risk of determining invalid conclusions, which need to be controlled by Benjamini-Hochberg FDR, covariates or be additionally tested in a subsample and validated by another subsample (known as split-sample validation).

Nevertheless, certain other limitations need to be considered. First, there are methodological difficulties involved in measuring loneliness. Loneliness is a subjective construct; in the context of depression, cognitive and affective distortions can occur, thus indicating that there is a risk that people with severe depression will demonstrate a more negative assessment. Another methodological limitation is that the measures used to assess the constructs of loneliness and depression may lack discriminant validity. An exploratory factor analysis could highlight such overlaps in a salient manner. In addition, the adapted German Social Network Index used in this study has not been formally validated; potential measurement bias cannot be excluded, and analyses based on this instrument are therefore exploratory. Interpretation is further complicated by the differing dimensionality of the instruments used to measure the construct of loneliness: whereas the 3-Item UCLA Loneliness Scale is unidimensional, the 6-Item DJGLS is bidimensional, which may affect how the relationship between loneliness and depression is understood. Although the scales are well-established and used in various countries and cultural contexts, the present sample is probably too small in size to examine cultural influences on the experience of loneliness or the tendency toward socially desirable responses, making biases possible. Altered response behavior may also occur due to repeated assessments (which is known as measurement reactivity) (98). These limitations can only be partially overcome by considering random effects of depression and loneliness and by varying the frequency of loneliness measurements during the study design phase (involving the use of the 3-Item UCLA Loneliness Scale every two weeks and the 6-Item DJGLS at three main measurement points). Self-selection bias may also be a potential limitation, thus indicating that patients with specific levels of loneliness or depression are more likely to participate; moreover, the representativity of the sample in terms of age or sex may be limited. Where available, reasons for non-participation will be reported transparently. Second, several analyses are explicitly exploratory and hypothesis-generating rather than confirmatory. In particular, the ROC-based cutoffs for response and relapse prediction are derived from the present sample and therefore subject to optimism bias; the resulting sensitivity, specificity, and threshold estimates require external validation before any clinical use. Likewise, biomarker and microbiome analyses rest on a site-restricted convenience subsample (biosampling at the University Hospital only) and are interpreted only as preliminary, generalizability-limited findings. This subsample may differ systematically from participants recruited at the community hospital in terms of illness severity, comorbidity profiles, or sociodemographic characteristics, as university hospital populations tend to include more treatment-resistant or complex cases. To mitigate false-positive results across the exploratory analyses, p-values are adjusted using the Benjamini–Hochberg false discovery rate, and key findings are, where feasible, examined by split-sample validation. To evaluate the comparability of both recruitment sites, baseline characteristics will be compared descriptively across centers, and the primary mixed model analyses will include study site as a covariate. Importantly, the primary hypotheses rely exclusively on clinical interview and self-report data (MADRS and 3-Item UCLA; additionally, PHQ-9 and 6-Item DJGLS) that are collected at both sites, ensuring that the main study objectives are testable independently of biomarker availability. Third, despite the longitudinal design of the study, the primary mixed model analysis of this initial non-interventional study on the association of loneliness and depression and their clinical relevance comes with the limitation of reverse causality.

Given that the study design does not permit definitive causal conclusions to be determined about the direction of all fixed and random effects, the findings are still expected to provide valuable insights and relevant implications. In particular, the following insights can be obtained (1): a report on whether patients with different levels of loneliness receive equal benefits from inpatient multimodal depression treatment; (2) insights into changes in loneliness during and after depression treatment; (3) important preliminary findings regarding the shared and distinct biopsychosocial mechanisms underlying loneliness and depression; and (4) the relationship of loneliness and depression on to secondary outcomes, including quality of life and suicidality.

Should the primary hypotheses be confirmed — that is, if baseline loneliness, change in loneliness or their interaction is significantly associated with the level of depressive symptom severity across the treatment course — this may carry implications for clinical practice. First, a brief loneliness screening (requiring less than two minutes using the 3-Item UCLA Loneliness Scale) might be considered for integration into routine psychiatric admission assessments, as it may enable clinicians to identify patients at risk for poorer treatment outcomes early in the treatment process — though randomized controlled studies would be needed to determine whether such screening translates into improved clinical outcomes. Second, the exploratory distinction between more situational and more enduring aspects — examined here only descriptively and without a validated state-trait measure — may, if associated with the course of depressive symptom severity, generate hypotheses for future interventional studies. Such studies could evaluate whether loneliness-focused components (e.g., cognitive restructuring of maladaptive social cognitions or facilitated social re-engagement during the transition from inpatient to outpatient care) add value to multimodal depression treatment. Any inference about modifiability would require an interventional design and lies beyond the scope of the present observational study. Third, the finding that loneliness at discharge predicts relapse would underscore the importance of addressing social connectedness as part of discharge planning and aftercare, a dimension that is currently underrepresented in German psychiatric treatment guidelines.

Several design features strengthen the evidential value of this study. The bicentric recruitment across a university hospital and a community psychiatric hospital enhances ecological validity by capturing a broader spectrum of clinical severity, treatment cultures, and patient populations than a single-site design would permit. The longitudinal design with three main assessment points and biweekly interim measurements allows for the modeling of individual symptom trajectories rather than relying on pre-post comparisons alone. The multimethod approach — combining clinician-rated interviews (MADRS), validated self-report instruments (PHQ-9, 3-Item UCLA Loneliness Scale and 6-Item DJGLS), biological sampling, and routine clinical data — reduces shared method variance and enables triangulation of findings across measurement modalities. Furthermore, the integration of both established loneliness scales alongside a newly developed state-trait item allows for the examination of construct-level questions that cannot be addressed with a single instrument.

Regarding generalizability, the study population comprises adults with a primary diagnosis of depression admitted to inpatient psychiatric care in a German metropolitan area. This setting reflects the structure of the German psychiatric care system, in which inpatient treatment typically involves multimodal therapy programs of several weeks’ duration — a model that differs substantially from shorter inpatient stays common in other healthcare systems (e.g., the United States or the United Kingdom). Consequently, the absolute effect sizes observed in this study may not be directly transferable to outpatient, day-clinic, or primary care settings, where treatment intensity, social context, and the natural course of both depression and loneliness may differ considerably. Similarly, the predominantly German-speaking sample and the use of German-language instruments limit the cultural generalizability of the findings, particularly given that the subjective experience and social determinants of loneliness are shaped by cultural norms regarding social contact and emotional disclosure. Nevertheless, the core research question — whether loneliness is associated with depression treatment outcomes — is relevant across healthcare systems, and the present study is intended to provide an empirical foundation that can be tested for replicability in other clinical populations and care settings. Therefore, the results may provide an evidence base and rationale for future clinical trials evaluating new treatment approaches in future intervention studies addressing loneliness in depression. Meta-analytic findings indicate that psychological interventions, especially cognitive-behavioral strategies targeting social cognition, can alleviate loneliness (99), underscoring their potential relevance for therapeutic approaches in depressive disorders. Furthermore, this study will contribute to a better understanding of the mechanisms linking loneliness and depression.

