
As empirical assumptions for the interplay between depression and loneliness in the inpatient and follow-up depression therapy are rare, we decided to set a change of 2 points in the MADRS per 1 SD of loneliness (3-Item UCLA Loneliness Scale) as the minimum meaningful association that shall be detected via the interaction (baseline x change) over the inpatient and post-treatment course. The model tested baseline loneliness and change in loneliness with at least 1.75 points MADRS as we have no empirical assumptions about which association is more significant for this setting, but we have a theoretical assumption that these single associations are less significant than their interaction. An omnibus likelihood ratio test will evaluate these assumptions in a single model, followed by Holm-Bonferroni corrected single tests to evaluate these three assumptions. This step will also evaluate the direction of effects and theoretical plausibility (more loneliness at baseline and less change in loneliness shall predict higher depressive symptom severity). The primary analysis of the linear mixed model includes all three measurement points as a categorial factor. Potential time- effects will serve as covariates in this model and will be reported exploratory with no influence on sample size calculation. Studies examining the clinical course of inpatient depression treatment measured with the MADRS report partly comparable values of MADRS at baseline (≈ 30 points) (62–64) and discharge, though findings remain heterogeneous (65, 66). Model assumptions for this sample size calculation were therefore based on plausible clinical values: T0 = 30, T1 = 16, T2 = 15 MADRS points, with a constant standard deviation of *SD* = 8 across all time points. Between-person differences in depression symptom severity (MADRS) were considered with fixed and random slopes, and ICC was set at .50. Power simulation involved assumptions of approximately 5% missing completely at random (MCAR) and 10% missing at random dropout at T2 (MAR). Sample size estimation was performed with R using the following packages: lme4, lmerTest, MASS and tidyr. The simulation for the overall model yielded a statistical power of ≥ 80% for all three assumptions at *n* = 172 with 15% combined dropout rate (MCAR, MAR), resulting in a total of *n* = 199. The number of simulations was 500 (nsim = 500) at a significance level of *α* = 0.05 for the omnibus likelihood-ratio test, with Holm-Bonferroni corrected single hypothesis tests. As depression can lead to cognitive distortion, correlations between loneliness and depression might be dependent on the measurement point, and given the insufficient clinical validation of the loneliness measures, it remains unclear whether the assumptions of a normal distribution and the assumed level of measurement adequately describe the interplay between depression and loneliness. Additional statistical methods are employed in an explorative and descriptive manner (generalized linear mixed-effects model and mixed analysis of variance). Power-analysis for mixed ANOVA using G*Power Version 3.1.9.7, with categorical groups of ‘high’ and ‘low’ loneliness (median-split) when considering an α error of 0.05, a power of 0.9 (1-β error probability) and a correlation value among repeated measures of 0.5 for the group’s results an estimated sample size of *n* = 36 participants assuming a medium effect size (*f* = 0.25), and *n* = 214 participants assuming a small effect size (*f* = 0.10).

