
To ensure the external validity of the results, it is important that both severely lonely depressive patients and less lonely depressive patients, as well as different disease trajectories and patient characteristics (e.g., age, sex, and number of comorbidities), can be identified. A sample size of approximately 200 participants is expected to ensure sufficient heterogeneity. This sample size is feasible in practice, since even taking into account an inclusion rate of 50% and a dropout rate of 30% for the primary diagnosis of depression at the University Hospital and the Community Hospital in Erlangen, the recruitment potential significantly exceeds the target number of cases within an estimated period of no more than two years.

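### Split-sample validation is the only internal check named for key exploratory findings; at about 170 completers, full-sample resampling (ROC) and the planned FDR control (associations) are more efficient

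*Protocol article*

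**What the plan says.** Split-sample validation appears twice in the protocol article, both times in the Discussion. The opening paragraph lists ways to guard against invalid conclusions from secondary outcomes and biosamples: Benjamini-Hochberg FDR, covariates, or that findings "be additionally tested in a subsample and validated by another subsample (known as split-sample validation". The limitations paragraph, after describing the FDR adjustment, adds that "key findings are, where feasible, examined by split-sample validation". It gives the purpose as limiting false positives across the exploratory analyses.

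Shortly before that, the same paragraph says the ROC cutoffs are "derived from the present sample and therefore subject to optimism bias" and need external validation before clinical use. The Statistical analysis section makes a similar point. Neither place names a full-sample internal correction such as the bootstrap or cross-validation. No split ratio is given, and no criterion for when a split counts as feasible.

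On sample size, the power simulation reached its target "at *n* = 172 with 15% combined dropout rate (MCAR, MAR), resulting in a total of *n* = 199", with missingness of "approximately 5% missing completely at random (MCAR) and 10% missing at random dropout at T2 (MAR". The feasibility paragraph also allows for "a dropout rate of 30% for the primary diagnosis of depression".

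**The concern.** A split divides a sample that is already modest for ROC work. The relapse endpoint is the scarcer of the two ROC outcomes. It also bears on practice: the Discussion draws implications for discharge planning and aftercare from loneliness at discharge predicting relapse. If the only internal check on that result rests on about 20 events, the check will be imprecise.

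The same holds for associations in the biosample subset, which is smaller than the full cohort because only the University Hospital collects samples. More efficient full-sample methods exist for both kinds of finding, and one of them is already in the plan.

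**Working it through.** **Sample available.** From the Sample size section: 172 analysable, 15% combined dropout, 199 enrolled. Check: 172/0.85 = 202.4; 172 × 1.15 = 197.8; 172/(0.95 × 0.90) = 201.2. All are within 3% of 199, so the stated figure is reproduced closely enough. Expected completers: 199 × 0.85 = 169, or 199 × 0.95 × 0.90 = 170. A 50:50 split (assumed) leaves about 85 per half. At the 30% dropout used for feasibility, 199 × 0.70 = 139, or about 70 per half.

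**Event rates.** Inputs from the plan: MADRS means 30, 16 and 15 at T0, T1 and T2; SD 8; ICC .50; and the response and relapse definitions. Assumptions: normal scores, and a correlation between visits equal to the ICC.
- Relapse, T2 ≥ 22: 1 − Φ((22 − 15)/8) = 1 − Φ(0.875) = .191.
- Relapse, rise ≥ 10: the change has mean −1 and SD √(64 + 64 − 64) = 8, so 1 − Φ(11/8) = .085.
- Either condition, under the bivariate normal: .231. That is 39 events in 170, or 19 to 20 per half.
- Response (T1 ≤ half of T0): T1 − 0.5·T0 has mean 1 and variance 64 + 16 − 32 = 48, so Φ(−1/6.93) = .44. That is 75 in 170, about 37 per half.

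**Precision of the AUC.** Hanley-McNeil standard error at an assumed AUC of .65; the half-width is 1.96 × SE.

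| Endpoint | Full sample | Half sample |
|---|---|---|
| Relapse (39/131; 19/66) | SE 0.053, ±0.10 | SE 0.075, ±0.15 |
| Response (75/95; 37/48) | SE 0.043, ±0.08 | SE 0.061, ±0.12 |

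For relapse, the half-sample interval runs from about .50 to .80.

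**Cutoff performance.** Simulation at n = 170 on an integer score from 3 to 9, with the cutoff chosen by the Youden index (1000 data sets, 100 bootstraps each). Assumed AUC 0.62 or 0.68; event rate 25% or 50%. Ranges are over these four scenarios.

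| Estimate of the Youden index | Bias | RMSE |
|---|---|---|
| Uncorrected | +0.037 to +0.055 | 0.073 to 0.084 |
| Bootstrap-corrected, full sample | +0.005 to +0.014 | 0.068 to 0.077 |
| 50:50 split | about 0 | 0.098 to 0.116 |

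A separate recomputation gave 0.079 for the bootstrap and 0.118 for the split. The split's SD is about 1.4 to 1.6 times the bootstrap's. With no true signal (AUC 0.50) the biases were +0.062, +0.021 and +0.005 respectively.

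**Associations.** Take an effect with 80% power in the full sample at two-sided 0.05: expected z = 1.96 + 0.84 = 2.80.
- In a half: 2.80/√2 = 1.98, power Φ(1.98 − 1.96) = .51. In both halves: .508² = .26.
- False-positive rate of that rule: 0.05² = 0.0025.
- One full-sample test at 0.0025: critical value 3.02, power Φ(2.80 − 3.02) = .41.

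For a correlation of .30 (Fisher z, 170 against 85 per half) the figures are 64% for both halves and 84% for the full-sample test at 0.0025. A more favourable split rule, with the second half tested one-sided at 0.05, also has a false-positive rate of 0.0025. It reaches 70%, still below 84%.

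**The case against.** The strongest reply is that the split is optional, exploratory and aimed at false positives, not at ROC optimism. Optimism correction does not control false-positive associations, so replacing the split by a bootstrap everywhere would leave that purpose unserved. This stands, and it is why the remedy must differ by type of finding. For associations, the full-sample counterpart is the FDR control already planned.

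Several stronger readings are tempting, and the documents or the figures do not support them:
- That the reported cutoffs would come from half the data. The article says they are derived from the present sample; the split is an added examination. Its application to ROC results is inferred from their being among the exploratory analyses.
- That the split costs 80% against 26% power. This compares one test at 0.05 with two. The like-for-like contrast is 41% against 26%, and the plan does not state a rule requiring significance in both halves.
- That true findings would usually fail to replicate. For a correlation of .30, power is 80% in each half.
- That a split says nothing usable about optimism. It is nearly unbiased; its weakness is variance.

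It can also be said that the feasibility qualifier lets the investigators skip an uninformative split, and that resampling detail belongs in the analysis plan. The first carries limited weight because no criterion is stated. The second does not remove the point, because the article does name a method and chooses the less efficient one.

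**Conclusion.** The point holds as a minor improvement. For ROC cutoffs and prediction results, a full-sample correction removes most of the optimism with clearly less error than a split: RMSE of about 0.08 against 0.12 at event rates near that expected for relapse. For associations, full-sample testing has more power at equal false-positive control. The loss is greater in the one-site biosample subset, whose size the article does not give.

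The figures rest on an assumed 50:50 split, normal MADRS scores, a correlation of .50 between visits, and assumed AUCs and simulation event rates. The direction was the same in every scenario with a true signal. The primary mixed model is not split, so its test and power are untouched. Nothing here replaces the external validation that the article already calls for.

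**What to change.** In the Discussion, and in the analysis plan where the exploratory methods are set out:
- **ROC cutoffs and any prediction model:** replace the split with bootstrap optimism correction, repeating the cutoff selection in each resample, or with repeated k-fold cross-validation on the full sample. Report corrected AUC, sensitivity and specificity, and the bootstrap distribution of the chosen cutoff.
- **Biomarker, microbiome and other associations:** rely on the planned Benjamini-Hochberg adjustment on the full available sample and drop the split.
- **Retain** the statement that external validation is required.

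The cost is wording and computing time; no new data are needed. The statistical price is a little residual optimism, about +0.01 in the Youden index when there is some true signal and about +0.02 when there is none.

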### Statistical analysis

2.6

To perform the statistical analysis, IBM SPSS Statistics Version 29 (96) and R (97) are used. To address the primary objective of this study, which is to examine the clinical relevance of the interplay between loneliness and depression in an inpatient and post-inpatient treatment setting, a set of statistical approaches is employed. To address the primary hypothesis, a linear mixed model with likelihood ratio test will be conducted to test against the null hypothesis that baseline loneliness, change in loneliness or their interaction have no additional association with the symptom severity in the course of depression (T0, T1, T2). In the primary linear mixed-effects model, depressive symptom severity (MADRS) is modeled across the three main assessment points (T0 = admission, T1 = discharge, T2 = three-month follow-up), with time entered as a categorical factor. Baseline loneliness at T0 (applied to T0, T1, and T2), the change in loneliness from admission to discharge (applied to T1 and T2), and their interaction (baseline × change) are entered as fixed effects, alongside random intercepts and random slopes capturing individual differences in symptom level and course. Because the length of inpatient stay differs between participants, the individual inpatient treatment duration (days from admission to discharge) is included as a time-related covariate rather than assuming a fixed interval between T0 and T1. The biweekly interim assessments are not part of the primary model and are reserved for the exploratory within-/between-person trajectory analyses described below. The primary test is an omnibus likelihood-ratio test of the null hypothesis that baseline loneliness, change in loneliness, and their interaction jointly show no association with the course of depressive symptom severity; only if this omnibus test is significant are the three individual coefficients examined, with Holm–Bonferroni correction. The formal model specification and the complete list of covariates are provided in the **Supplementary Material** (Section 4 and **Supplementary Table S1**). All models will be controlled for time-effects (e.g., length of inpatient treatment duration), measures obtained at the same timepoint (e.g. explorative analysis of measurement specific associations of loneliness and depression), recruitment site, gender and age and will be tested for further covariates such as social anxiety and social support. The primary analysis sample will include all participants who completed T0 and T1 depression severity measures (MADRS) and loneliness measures (3-Item UCLA). For each questionnaire, missing individual data points are imputed using person-mean imputation, provided that no more than 20% of the data is missing. Participants with an inpatient stay shorter than seven days (post-enrollment exclusion criterion) are not part of the primary analysis set, since no discharge assessment (T1) is obtained for them; where baseline (T0) data are available, they are retained in the sensitivity analyses of all available data. The extent and pattern of missing values will be described for all inference statistical analysis. Given that dropout is likely associated not only with observed characteristics (MAR) but also with unobserved post-discharge symptom severity (MNAR), sensitivity analyses will include pattern-mixture models or selection models to evaluate the robustness of primary findings under MNAR assumptions. As a pragmatic benchmark, a worst-case analysis will be performed assuming that all dropouts at T2 experienced no improvement (last observation carried forward) or deterioration (fixed offset of +5 MADRS points).

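### As the article describes it, site adjustment removes only a constant MADRS difference between the hospitals, so a site difference in course can leak into the change-in-loneliness coefficient; a site-by-time term would prevent this at almost no cost

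*Protocol article*

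**What the plan says.** The Statistical analysis section sets out the primary linear mixed model for MADRS at T0, T1 and T2, "with time entered as a categorical factor". Two loneliness terms are coded differently over time. The first is a level effect: "Baseline loneliness at T0 (applied to T0, T1, and T2"). The second acts after admission only: "the change in loneliness from admission to discharge (applied to T1 and T2"). Their product and random intercepts and slopes are added, and length of stay "is included as a time-related covariate rather than assuming a fixed interval between T0 and T1". The primary test is a joint likelihood-ratio test of the three loneliness coefficients.

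On site, the same section lists adjustment for "recruitment site, gender and age and will be tested for further covariates such as social anxiety and social support". The Discussion repeats that "the primary mixed model analyses will include study site as a covariate", and plans a descriptive comparison of baseline characteristics between centres. The formal specification and full covariate list are referred to the Supplementary Material (Section 4 and Table S1), which is not shown.

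On how the hospitals may differ, the Discussion remarks that "university hospital populations tend to include more treatment-resistant or complex cases", and counts as a strength of two-site recruitment that it enhances ecological validity by "capturing a broader spectrum of clinical severity, treatment cultures, and patient populations than a single-site design would permit".

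**The concern.** A site main effect removes one MADRS difference that is the same at all three visits. It cannot represent a hospital difference in how far MADRS falls. That difference lies on the contrast between T0 and T1/T2, which is where the change-in-loneliness term operates. If loneliness also falls further at one hospital than at the other, the change term becomes a partial proxy for hospital.

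A difference in course is plausible on the protocol's own remarks: treatment resistance concerns response, and treatment culture concerns what happens after admission. The Data collection section adds that the patient's own treatment team rates the MADRS, so raters are nested in hospital. A constant rating difference is removed by the site covariate; one that varies over the stay is not.

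At stake is the single confirmatory test. Part of a significant result could reflect hospital rather than loneliness, and the planned between-site comparison, limited to baseline, would not show it.

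**Working it through.** **Inputs from the Sample size section.** n = 172 analysed; MADRS means 30, 16, 15; SD 8; ICC 0.50; target effects of 1.75 points for baseline and for change, and 2 points for their product.

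**Reproducing the plan's figures.** 172 × 1.05 × 1.10 = 198.7, or 199, as stated. Simulating the stated model at n = 172 (random intercept, 500 runs) gives Holm-adjusted power of 0.90 / 0.97 / 0.98 for baseline, change and product. With an assumed random-slope SD of 4 it is 0.87 / 0.88 / 0.93. This agrees with the stated power of at least 80%, so the check starts from the plan's own model.

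**Assumptions not in the document.** Sites split 50:50. D is the site difference in MADRS fall, in points. d is the site difference in mean loneliness change, in SD units. Baseline and change in loneliness are independent, and all true loneliness effects are zero.

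**Closed form for the bias.** SD 8 and ICC 0.5 give a between-person and a residual variance of 32 each. Code site as ±0.5 (variance 1/4) and write change as d × site + e, with var(e) = v. Let p = (0, 1, 1) be the coding of the change term and 1 = (1, 1, 1) that of a site main effect. With V the covariance matrix of the three visits:

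- A = p′V⁻¹p = 1/32
- B = p′V⁻¹1 = 0.5/32
- C = 1′V⁻¹1 = 0.75/32
- k = 1 − B²/(AC) = 1 − 0.25/0.75 = 2/3, the share of the site-course contrast that a site main effect leaves unadjusted

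Minimising the generalised least-squares criterion over the change and site coefficients gives

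bias = D × (k·d/4) / (v + k·d²/4).

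Its sign is that of D × d, and it is zero when d = 0. Example with D = 4, d = 0.5, v = 1: 4 × 0.0833 / (1 + 0.0417) = 0.32 points.

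**Omnibus error.** SE² = 32 / [172 × (v + k·d²/4)]. In the example this is 32 / (172 × 1.0417) = 0.1786, so SE = 0.423 and λ = (0.32/0.423)² = 0.57. The chance that a noncentral chi-square on 3 df with this λ exceeds 7.815 is 8.6%.

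| D (points) | d (SD) | Bias, formula | Error, formula | Simulation (bias; error) |
|---|---|---|---|---|
| 4 | 0 | 0 | 5.0% | 0.01; 5.5% |
| 2 | 0.25 | 0.08 | 5.2% | 0.11; 5.3% |
| 3 | 0.3 | 0.15 | 5.7% | error about 6% |
| 2 | 0.5 | 0.16 | 5.9% | 0.17; 6.8% |
| 4 | 0.5 | 0.32 | 8.6% | 0.31; 8.4% and 0.34; 8.8% |
| 4 | 0.8 | 0.48 | 14.4% | 0.48; 13.6% and 0.57; 16.9% |

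Simulations used 800 or 2,000 runs. With 800 runs the Monte Carlo SE of an error rate near 5% is about 0.8 percentage points. In the last row, most of the gap between the two simulated biases matches the choice of SD. Taking the SD over the whole sample rather than within hospital sets v = 1 − d²/4 = 0.84, and the formula gives 4 × 0.1333 / (0.84 + 0.1067) = 0.56.

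**Random slopes.** The plan has them, so they were added on the post-admission contrast (SD 4 or 6, assumed; 2,000 runs). At 4 points and 0.5 SD, bias was 0.39 and 0.43 and error 9.8% and 8.0%. At 4 points and 0.8 SD, bias was 0.63 and 0.70 and error 14.6% and 12.8%. Random slopes do not remove the leakage.

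**With site by time added.** Without random slopes, bias was −0.02 to 0.03 and error 4.6% to 6.5%. With them, bias was within 0.03 and error 4.5% to 5.4%, and the SD of the change coefficient rose by at most about 6%.

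**The case against.** The strongest reply is that the omission is not proven. The article defers the formal model to a supplement, and whether a covariate also interacts with time is a detail an article may leave there. This stands. The point is therefore about the model as the article describes it, and the first step is to check the supplement.

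A reader might also infer that the protocol expects the hospitals to differ in course and that the change term will absorb the difference. The documents do not support that. The wording is that the University Hospital biosample subsample may differ and that such hospitals tend to have resistant cases; treatment cultures are named as a strength. No statement says that loneliness change differs by site, and without that the bias is zero. Even then only part of the difference transfers.

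The size also rests on assumed figures, and 4 points is a large site gap against a planned fall of 30 − 16 = 14. With slope variation and an unstructured covariance (2,000 runs), the error at 4 points and 0.5 SD was 6.5–7.6%, against 5.5–6.3% with no site difference. It reached about 10–14% only at 4 points and 0.8 SD.

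Length of stay is already in the model, and the sensitivity analyses allow further covariates and confounders, so part of a site difference may be adjusted that way. The article also disclaims causal conclusions. These arguments limit the importance of the point. They do not change the fact that a constant site effect cannot adjust for a difference in course.

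**Conclusion.** The point holds conditionally. The site adjustment named in the article cannot remove a hospital difference in MADRS course from the change-in-loneliness coefficient. Harm requires a second site difference, in mean loneliness change, which the article neither states nor excludes.

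Under the assumed 50:50 split, modest differences (2–3 points, 0.3–0.5 SD) give a bias of about 0.15–0.2 points and an error rate of about 5–6.5%, close to nominal. At 4 points and 0.5 SD the figures are about 0.35 points and 7–9%. At 4 points and 0.8 SD they are about 0.5 points and 12–15%, with 10–17% across all model variants tried and bias up to 0.7 points with random slopes. All of these biases are well below the 1.75-point target. They do not show that a positive result would be a hospital artefact, nor that the supplement's model lacks the term. The calculations leave out length of stay, age and gender as covariates.

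The change is still worth making: it protects the only confirmatory test with a variable already collected, at almost no cost.

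**What to change.** Check the formal specification in Supplement Section 4. If site by time is not there, add site by categorical time to both the null and the full primary model, so that the omnibus test still compares models differing only in the three loneliness terms. State this in the Statistical analysis section. Alongside the planned baseline comparison of centres, report the T0-to-T1 change in MADRS and in the 3-item UCLA scale by site, so that readers can see whether both conditions for bias are present.

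The cost is two extra parameters and one descriptive table. The sample size does not change, and the loss of precision in the change coefficient was at most about 6% in the scenarios tried.
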